## RapidNSTEMI Biomarkers v1.0

[figure not shown]

Professor of Cardiology, Honorary Consultant  
Cardiologist  
King's College London  
Guy's & St Thomas' Hospitals  
The Rayne Institute, St Thomas' Hospital  
[name]  
Email: [[contact]](mailto:[contact])

[name]  
Professor of Interventional Cardiology  
Wessex Cardiothoracic Unit  
Southampton University Hospitals NHS Trust  
[name]  
Email: [[contact]](mailto:[contact])

RapidNSTEMI Biomarkers v1.0

[figure not shown]

1. Introduction

Cardiac troponin (cTn) is now well established as a biomarker of myocardial injury and therefore a critical component in the diagnosis of acute coronary syndrome (ACS), as outlined in the Fourth Universal Definition of Myocardial Infarction (1). Although contemporary high-sensitivity troponins have demonstrated increasing sensitivity for myocardial injury (2), they are widely recognised to be organ-specific rather than disease-specific (3).

Hence, in the acute setting clinicians are repeatedly required to distinguish whether ischaemic or non-ischaemic injury has occurred from the clinical history alongside electrocardiogram (ECG) interpretation. Since ECG changes are found in only 40% of patients diagnosed with non-ST elevation myocardial infarction (NSTEMI) or unstable angina (4), major inconsistencies in the diagnosis of acute myocardial infarction remain a significant problem (5). Furthermore, a recent observational study that measured high-sensitivity troponin (hs-Tn) in 20,000 consecutive patients (in-hospital or outpatient) has raised important questions about the use of the manufacturer-supplied 99th centile as an upper limit of normal threshold with which to diagnose myocardial infarction, as the 99th centile was found to be 6 times the manufacturer derived value (6). Therefore, biomarkers sensitive and specific to degrees of myocardial injury with a defined upper limit of normal appropriate to a hospital population would be a valuable contribution to the clinical arena.

Although elevated cTn levels indicate injury to myocardial cells, they do not reflect the underlying pathophysiological mechanisms and can arise due to a variety of non-ischaemic cardiac and non-cardiac disease processes (7). Improvements in assay sensitivity have lowered diagnostic thresholds but at the expense of reduced specificity, thus leading to diagnostic uncertainty, particularly in the context of uncertainty with regard to assay-specific thresholds for abnormality.

There is therefore a need for novel cardiac biomarkers with superior specificity to provide greater diagnostic capability in patients presenting with recent onset cardiovascular symptoms. These biomarkers may also have a significant role to play in risk stratification and long term prognosis of patients diagnosed with ACS (8).

Desired characteristics of an ideal cardiac biomarker are listed in Table 1.

Table 1

| Characteristics of an ideal cardiac biomarker                             |
|---------------------------------------------------------------------------|
| 1. High sensitivity                                                       |
| 2. High specificity                                                       |
| 3. High myocardial concentration and absence in non-myocardial tissues    |
| 4. Rapid release into blood and bodily fluids following myocardial injury |
| 5. Rapid clearance from blood and bodily fluids                           |
| 6. Detection by simple, rapid, and cost-effective assays                  |

## RapidNSTEMI Biomarkers v1.0

[figure not shown]

7. Well validated threshold differentiating between normal (healthy) and abnormal (disease state positive)

The RapidNSTEMI main study is a prospective randomised controlled trial designed to test the hypothesis that very early angiography with, where appropriate, revascularisation in higher-risk NSTEMI patients will improve clinical outcomes compared with standard care.

The Biomarkers substudy is designed to assess the levels of novel biomarkers in this higher risk NSTEMI population, thereby allowing direct comparison with measured contemporary hs-Tn. Subsequent correlation of these biomarkers with clinical outcomes, and investigation into their potential as predictors of coronary artery disease requiring PCI, will also be assessed to determine whether they are candidates to improve future clinical stratification and triage. Additionally, the unique aspect of participant randomisation to differing treatment strategies will allow direct evaluation of novel biomarker release according to timing of PCI and the impact of procedural related injury on outcomes. Such analyses may allow the identification of these new biomarkers as plausible candidates to refine care pathways in the future.

## 2. Biomarkers

The RapidNSTEMI Biomarkers substudy will investigate three novel candidate biomarkers that have potential to improve the sensitive and specific detection of ACS, and aid in its risk stratification.

1. **Cardiac myosin-binding protein C (cMyC)** is a cardiac-specific protein showing early promise as a novel biomarker of myocardial injury. Released more rapidly than hs-Tn T or I, cMyC has been shown to provide similar diagnostic accuracy for acute myocardial infarction. However, it may be superior in patients presenting early after symptom onset (9). Use of cMyC as a predictor of long-term survival has suggested comparability to hs-Tn T, and superiority to hs-Tn I (9).
2. **Growth differentiation factor-15 (GDF-15)** is a member of the transforming growth factor beta superfamily (TGF- $\beta$ ) that have been shown to become upregulated in response to oxidative stress, inflammation and tissue injury; all of which occur in myocardial infarction. (10). Previous studies have demonstrated a good correlation with the level of Global Registry of Acute Coronary Events (GRACE) score (11), and superior prediction of major bleeding and cardiovascular events, even when a single measurement of GDF-15 is taken (12).
3. **Suppression of tumorigenicity-2 (ST-2)** is a member of the interleukin-1 (IL-1) receptor family upregulated in myocardial strain, and is suggested to be part of the acute inflammatory response to myocardial injury and infarction (13). Data have demonstrated that levels are increased in NSTEMI and associated with a greater than two-fold increased risk of mortality at 12 months (OR 2.3 [95% CI 1.1-4.6],  $P=0.03$ ) (14).

## RapidNSTEMI Biomarkers v1.0

[figure not shown]

### **3. Aims of substudy**

The RapidNSTEMI Biomarkers substudy aims to explore the association between hs-Tn, the tested novel biomarkers, and clinical outcomes in higher-risk NSTEMI patients recruited to the main RapidNSTEMI trial.

Primary aim:

- To investigate in patients with a clinical diagnosis of NSTEMI, the sensitivity and specificity of novel biomarkers (cMyC, GDF-15 and ST-2) in predicting which patients do or do not require PCI following diagnostic angiography.

Secondary aims:

- Correlate levels of each biomarker with cTn taken in the same patient
- Comparative predictive value of each biomarker for primary and secondary main trial outcome measures, and to include in-hospital, 30-day and 6-month rates of major adverse cardiovascular events
- Comparison between biomarkers for predictive values
- Impact of PCI on each biomarker release and subsequent future clinical outcomes
- Positive and negative prediction for type of myocardial infarction (Type 1, Type 2, Type 4a)
- Development of a multivariate model combining candidate biomarkers with risk stratification scoring criteria (e.g. GRACE score) to produce an optimal predictor of clinical outcome

### **4. Statistics and power calculations**

#### **Sample size**

With the available resources we will be able to collect and analyse two samples (pre and post-angiography) from 550 patients. It is expected that approximately two-thirds of patients in our cohort will require PCI. If we recruit 550 patients, we expect approximately 367 to require PCI and 183 to not. Based on these 550 patients, 80% power and a 5% significance level, we can calculate the following for the three novel biomarkers.

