#### 6.5 HYPOTHESIS TO BE TESTED

RAPID-NSTEMI will test the following hypothesis:

Immediate angiography with a view to follow on revascularisation in patients presenting with N-STEMI ACS and at higher risk (GRACE score  $\geq 118$  or  $\geq 90$  with additional high risk features), will result in a significant reduction in rate of major adverse clinical outcomes

RAPID-NSTEMI[figure not shown]

(death/MI/hospitalisation for heart failure) within 12 months compared with angiography with follow on revascularisation undertaken according to current standard of care.

Randomisation will take place prior to angiography, following GRACE 2.0 score assessment. At angiography it will become clear that a percentage of patients will require CABG (~8%), some will have normal coronary arteries and some will be treated medically but the analysis will be on an intention to treat (ITT) basis, since randomisation needs for logistical reasons to be undertaken prior to angiography. While the final analysis will be ITT, outcomes according to actual treatment received will also be reported separately as a “per treatment received” analysis.

This will be very important since it will test the hypothesis as to whether very early received intervention is better than current standard of care. Thus, a secondary analysis will be those who receive revascularisation at the time of very early angiography versus those who receive revascularisation at the timing of current standard of care.

We expect this to be a Guideline-informing, clinical practice-directing trial that will help direct clinicians as to the timing of PCI in N-STEMI ACS patients. The trial is didactic, simple, robust, and will be managed by experienced interventional trialists and a registered Clinical Trials Unit, all with a track record for trial delivery.

RAPID-NSTEMI[figure not shown]

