### ST-2

Based on data by Eggers et al (14), and estimating the standard deviation using Wan et al (15) to be 20, we will be able to detect a mean difference in ST-2 of 6U/ml between the groups. For ST-2, the 99th percentile cut-off point determined previously in a healthy reference population is 31U/ml in men and 21U/ml in women (18). Median levels in patients diagnosed with N-STEMI are 28U/ml with 45% of patients noted to have elevated levels at the point of diagnosis when taking into account gender-specific upper reference levels (14). Again, there are no available data in patients with non-obstructive coronary disease.

The above statistical calculations aim to provide power for the selected biomarkers to predict a clinically meaningful difference between the two groups in whom we are interested; those with obstructive coronary artery disease that require PCI following diagnostic angiography, and those that do not. This is a novel study, and consequently there is limited literature supporting the differences we are likely to see between these two groups. Any results are likely to be hypothesis generating. Despite this, we feel these differences are of clinical importance and hence our proposed sample size of 550 patients is sufficient for our aims.

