### Statistical analysis

Summary statistics including counts and percentages will be provided for all categorical variables and means and standard deviations for normally distributed continuous variables and medians and interquartile ranges for non-normally distributed continuous variables. The differences in the levels of the biomarkers between the two groups (PCI vs no PCI) will be initially analysed using a two-sample t-test. Appropriate transformations will be made to non-normally distributed variables. Subsequently, multiple linear regression will be performed to adjust for potential confounders (including age and sex). Adjusted means, mean differences, 95% confidence intervals (CIs) and p-values will be provided for comparisons across the two groups.

Based on the previous results showing significant differences between the groups for these novel biomarkers, Receiver Operating Characteristic (ROC) analyses will be performed in order to determine the optimal cut-off points for each biomarker for the requirement of PCI. That is, the cut-point which best provides the best balance between sensitivity (proportion of true positives) and specificity (proportion of true negatives) for the level of biomarker as a diagnostic tool. Sensitivities, specificities and area under the curves will be reported for these cut-offs.

In addition to the above analyses, correlations and comparisons will also be reported between these novel biomarkers and troponin. Clinical outcomes comparing those who do and do not require PCI will be analysed univariately and multivariately with logistic regression. All data will be analysed using the R environment for statistical computing (19).

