## RapidNSTEMI Biomarkers v1.0

[figure not shown]**Clinical implications**

Diagnostic coronary angiography currently attracts a National Health Service (NHS) tariff of £831 to £2239, dependent on patient co-morbidity and case complexity (20). Close to 250,000 diagnostic coronary angiograms are performed every year in the UK, with approximately 100,000 of these procedures subsequently proceeding to PCI (21). Therefore, identifying patients with non-obstructive coronary disease who do not require angiography through an appropriately sensitive and specific biomarker panel could result in significant healthcare cost savings, and limit unnecessary patient exposure to procedural risks.

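### As written, the biomarker sub-study scores patients sent for CABG as negatives, so its planned sensitivity, specificity and cut-off do not match the obstructive-disease outcome and use that the protocol gives for it

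*Protocol*

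**What the plan says.** Appendix VI, section 3, sets the primary aim as the sensitivity and specificity of cMyC, GDF-15 and ST-2 for predicting need for PCI after diagnostic angiography. Section 4 sizes the sub-study on the same split: "It is expected that approximately two-thirds of patients in our cohort will require PCI", and then "If we recruit 550 patients, we expect approximately 367 to require PCI and 183 to not". The closing paragraph under ST-2 describes the groups as "those with obstructive coronary artery disease that require PCI following diagnostic angiography, and those that do not". The analysis follows suit: "The differences in the levels of the biomarkers between the two groups (PCI vs no PCI) will be initially analysed" with a t-test, and the ROC cut-offs are chosen for requirement of PCI.

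Two other places describe a different target. Section 7.13 names prediction of obstructive coronary disease as a key outcome beside need for PCI. The Clinical implications paragraph of Appendix VI gives the eventual use as "identifying patients with non-obstructive coronary disease who do not require angiography through an appropriately sensitive and specific biomarker panel".

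The main protocol (section 6.5 and Appendix VII) expects about 8% of patients to need CABG. Appendix VII gives the reason as complex lesions or multi-vessel disease, and adds that some patients with diffuse disease will be treated medically. Nothing in Appendix VI excludes these patients or places them with the PCI group.

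**The concern.** A patient referred for surgery has obstructive disease and needed the angiogram. Under a PCI versus no PCI standard that patient is a negative. A high marker is scored as a false positive, and a low marker as a correct negative. For a test whose suggested use is to spare angiography, a low marker in a surgical patient is the error that matters most, and the planned analysis counts it as a success. The ROC cut-off would be tuned to separate PCI from a mixture of surgical, diffuse, non-obstructive and normal findings, which is not the split named in section 7.13 or under Clinical implications.

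**Working it through.** **Inputs.** N = 550, two-thirds PCI, 80% power and 5% significance (Appendix VI, Sample size; two-sided is assumed because the sides are not stated). SD and stated detectable difference: cMyC 430 and 132 ng/L; GDF-15 780 and 240 ng/L; ST-2 20 and 6 U/ml. CABG rate 8% (section 6.5, Appendix VII), varied here from 5% to 10%.

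**The plan's own figures.** 550 × 2/3 = 367 and 550 × 1/3 = 183, so the split reproduces and uses every patient. Detectable difference = SD × (1.96 + 0.84) × √(1/367 + 1/183), which gives 109, 198 and 5.1. The stated 132, 240 and 6 are larger, hence conservative: at 367 v 183 they have 91% to 92% power. That is a separate matter.

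**CABG patients among the negatives.** 0.08 × 550 = 44, and 44/183 = 24%. At 5% it is 27.5 patients (15%); at 10% it is 55 (30%).

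**Mean difference, if CABG patients have PCI-like levels.** Observed difference = (1 − CABG share of negatives) × true difference. For cMyC, 0.76 × 132 = 100. The standard error is 430 × √(1/367 + 1/183) = 38.9. Power is Φ(132/38.9 − 1.96) = 92% undiluted and Φ(100.3/38.9 − 1.96) = 73% diluted.

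| CABG rate | Observed difference | Power |
|---|---|---|
| 5% | 112 | 82% |
| 8% | 100 | 73% |
| 10% | 92 | 66% |

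**Accuracy, same assumption, 8% CABG.** Apparent specificity = (139 × specificity + 44 × (1 − sensitivity))/183.
- Sensitivity 80%, specificity 70%: (97.3 + 8.8)/183 = 58%. About 9 surgical patients with a low marker count as correct negatives.
- Sensitivity 90%, specificity 80%: (111.2 + 4.4)/183 = 63%.
- Sensitivity 90%, specificity 70%: the negative predictive value is 0.735 against PCI, but 0.704 against any revascularisation, so a negative result looks slightly safer than it is.

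**Regrouping CABG with PCI.** 367 + 44 = 411 v 183 − 44 = 139. The standard error for cMyC is 430 × √(1/411 + 1/139) = 42.2. Detectable differences are 118, 214 and 5.5, all below the stated 132, 240 and 6. Power for a true 132 is 88%.

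**How far the assumption matters (cMyC, 8% CABG, PCI mean 132 above the non-revascularised mean).**
- CABG mean midway (66 above): PCI v no PCI shows 132 − 0.24 × 66 = 116, power 85%. The regrouped difference is 132 − 66 × 44/411 = 125, power 84%.
- CABG mean equal to the non-revascularised mean: PCI v no PCI keeps 132, power 92%. The regrouped difference is 132 × 367/411 = 118, power 80%.

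The power gain from regrouping therefore depends on the assumption. The mismatch of target does not.

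**The case against.** The strongest reply is that the sub-study does what it says. Predicting need for PCI is the aim in section 7.1, section 7.2.2 and Appendix VI section 3, and the groups and ROC target agree with it. The Clinical implications paragraph looks ahead and states no hypothesis. The appendix itself calls results likely to be hypothesis generating. Angiography decisions are documented in the eCRF (section 7.8), so patients can be regrouped later. The 8% is a main-trial estimate, and nothing shows that CABG patients have PCI-like levels of markers that reflect injury, inflammation or strain.

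Much of this stands. It rules out three stronger readings that a reader might infer:
- That the sub-study cannot support any work on non-obstructive disease. The data allow a re-analysis; it is the written analysis that does not address it.
- That the accuracy measures will certainly be pulled down. That needs CABG patients to have raised levels, and the effect shrinks if their levels are lower.
- That Appendix VII puts medically treated diffuse disease at a few per cent. That figure refers to normal coronary arteries; none is given for diffuse disease.

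What does not stand is that this is detail for a later plan. Appendix VI itself fixes the aim, groups, test and ROC target, and section 7.13 names obstructive disease as an outcome for which the appendix defines no group or analysis.

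**Conclusion.** The point holds in a limited form. As written, the only reference standard is PCI versus no PCI, so about 44 of 550 patients, 24% of the negatives (15% to 30% at CABG rates of 5% to 10%), have surgical disease but count as negatives. That follows from the definition and the exhaustive split; the protocol does not say it outright. The resulting sensitivity, specificity and cut-offs describe need for PCI, and do not match the obstructive-disease outcome of section 7.13 or the use of sparing angiography. The losses in difference (132 to about 100), power (92% to 73%) and specificity (70% to about 58% at sensitivity 80%) are illustrations that rest on equal marker levels in CABG and PCI patients. A reader might go on to infer that an unsafe cut-off will enter practice. The documents do not support that: the sub-study is exploratory and proposes no cut-off for use. The main trial's primary result is not affected.

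**What to change.** In Appendix VI, section 4, run the group comparison and ROC analysis with revascularisation (PCI or CABG) decided at index angiography versus none as the reference standard. Restate the expected split as about 411 v 139, and keep PCI v no PCI as a secondary description. Align the primary aim with this.

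Regrouping alone leaves medically treated diffuse disease among the negatives. For the Clinical implications claim, therefore, take as the rule-out group the patients recorded as needing no further management because there was no flow-limiting obstruction, a decision listed in section 7.8. Otherwise, limit that claim to need for PCI. Section 7.8 does not say that stenosis severity is recorded, so a standard based on a percentage stenosis should not be assumed available.

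Cost: wording, one regrouped variable and one extra analysis, with no new patients or samples. The split is less even (88% power for a cMyC difference of 132, against 92% for an undiluted 367 v 183), but the detectable differences of about 118, 214 and 5.5 stay within those stated.

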#### **cMyC**

Based on data by Kaier et al (9), and estimating the standard deviation using Wan et al (15) to be 430, we will be able to detect a mean difference in cMyC of 132ng/L between the groups. For cMyC, the 99th percentile cut-off point determined previously in stable patients without obstructive coronary artery disease referred for invasive angiography is 87ng/L (16). Patients diagnosed with acute myocardial infarction were found to have median levels of 237ng/L (9).

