#### **GDF-15**

Based on data by Wollert et al (17), and estimating the standard deviation using Wan et al (15) to be 780, we will be able to detect a mean difference in GDF-15 of 240ng/L between

[figure not shown]University Hospitals of Leicester  
NHS Trust

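### Biomarker sub-study (Appendix VI): the three detectable differences do not follow from the stated inputs, and sensitivity and specificity are to be reported at cut-offs chosen on the same patients

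*Protocol*

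**What the plan says.** Appendix VI, section 4 (Sample size) starts from what resources allow, namely two samples from each of 550 patients. It expects about two-thirds to need PCI: "we expect approximately 367 to require PCI and 183 to not". The detectable differences are then worked out on this footing: "Based on these 550 patients, 80% power and a 5% significance level". The three results are:

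- cMyC, with an SD of 430: "we will be able to detect a mean difference in cMyC of 132ng/L between the groups".
- GDF-15, with the SD estimated "to be 780, we will be able to detect a mean difference in GDF-15 of 240ng/L between" the groups.
- ST-2, with an SD of 20: "we will be able to detect a mean difference in ST-2 of 6U/ml between the groups".

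The ST-2 subsection ends by judging 550 sufficient for the aims, and warns that the results will probably only generate hypotheses.

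The Statistical analysis subsection compares PCI with no PCI by a two-sample t-test, then by adjusted linear regression. ROC analysis then finds, for each marker, the cut-off with the best balance of sensitivity and specificity. "Sensitivities, specificities and area under the curves will be reported for these cut-offs". No split sample, resampling correction or external validation is mentioned. Sensitivity and specificity for need of PCI are the primary aim of the sub-study (Appendix VI, section 3) and a secondary outcome of the main trial (section 7.2.2).

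**The concern.** Appendix VI supplies every input to the detectable-difference calculation except whether the test is one- or two-sided, so the figures should be reproducible. All three miss by a similar proportion, which suggests one shared undeclared input and not three separate slips. A reader cannot tell which of N, alpha or usable samples was really meant.

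The second matter is bias. A cut-off picked because it gave the best result in these patients will look better in them than in new patients. Appendix VI (Clinical implications) looks ahead to a marker panel that could spare some patients angiography, so the reported accuracy should not be flattered by the way the cut-off was found.

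**Working it through.** **Inputs (Appendix VI, section 4).** n1 = 367, n2 = 183; power 80%; significance 5%; SDs 430, 780 and 20; two-sample t-test. Sidedness is not stated for the sub-study. I assume two-sided, as in protocol section 8.1, and also try one-sided.

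**Attempt to reproduce the printed figures.**

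Detectable difference = SD × (z for alpha + z for power) × √(1/n1 + 1/n2)

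- √(1/367 + 1/183) = 0.0905
- (1.960 + 0.842) × 0.0905 = 0.2535 SD (0.254 by the exact t-test solution)

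| Marker | SD | Printed | Recomputed (normal / t-test) | Printed ÷ recomputed | Power at printed difference |
|---|---|---|---|---|---|
| cMyC, ng/L | 430 | 132 | 109.0 / 109.2 | 1.21 | 92.4% |
| GDF-15, ng/L | 780 | 240 | 197.8 / 198.1 | 1.21 | 92.5% |
| ST-2, U/ml | 20 | 6 | 5.07 / 5.08 | 1.18 | 91.2% |

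The power column is Φ(difference ÷ (SD × 0.0905) − 1.960). For cMyC this is Φ(132 ÷ (430 × 0.0905) − 1.960) = Φ(1.43) = 92.4%.

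The printed figures do not reproduce. Rounding does not explain it: 5.07 does not round to 6, and the SDs would have to be about 521, 947 and 23.7 (printed difference ÷ 0.2535).

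**Other readings.**

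| Reading | cMyC | GDF-15 | ST-2 |
|---|---|---|---|
| Printed | 132 | 240 | 6 |
| One-sided 5% | 96.8 | 175.5 | 4.5 |
| Equal groups of 275 | 102.7 | 186.4 | 4.8 |
| Mann-Whitney, efficiency 0.864 | 117.3 | 212.8 | 5.5 |
| 20% sample loss | 121.9 | 221.1 | 5.7 |
| 30% sample loss | 130.3 | 236.4 | 6.1 |
| Bonferroni over three markers | 125.9 | 228.4 | 5.9 |
| 90% power | 126.1 | 228.8 | 5.9 |
| Alpha 0.01, two-sided | 133.0 | 241.2 | 6.2 |

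Nothing using the stated 5%, 80% and 550 patients gives the printed values. Solving for N at the same split gives about 376, 376 and 394 patients. For cMyC and GDF-15, that corresponds to losing about 32% of 550. Alpha 0.01 with all 550 comes nearly as close: 0.309 SD. It would give 132 and 240 if the unrounded SDs were about 427 and 776.

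**Cut-off optimism.** Data sets of 367 and 183 patients were simulated with normal markers of equal SD, taking the cut-off at the maximum of sensitivity + specificity. Apparent performance was compared with true performance at that same cut-off (2,000 data sets per effect size).

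| Standardised difference | AUC | Apparent sens + spec − 1 | True | Overstatement |
|---|---|---|---|---|
| 0 | 0.50 | 0.055 | 0.000 | 0.055 |
| 0.307 (printed cMyC) | 0.59 | 0.156 | 0.113 | 0.044 |
| 0.5 | 0.64 | 0.229 | 0.188 | 0.041 |
| 0.8 | 0.71 | 0.338 | 0.303 | 0.036 |
| 1.0 | 0.76 | 0.407 | 0.375 | 0.032 |

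At 0.307, apparent sensitivity and specificity average 56.5% and 59.2%, against true values of 54.9% and 56.4%.

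**The case against.** The arithmetic slip harms nothing in the design. Resources fixed 550, and the calculation only describes what that number can detect. With the correct figures, the sub-study detects smaller differences than claimed. This stands. A reader might infer that the sub-study is underpowered or that 550 loses its justification. The documents do not support that, because the error runs the other way.

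Nor can the fault be pinned on N. A reader might infer that the authors really computed for about 375 patients, but an alpha of 0.01 with all 550 explains the figures almost as well. It contradicts the printed 5%, so something must change, but only the authors can say what.

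On the cut-offs, an analysis plan not seen here might add internal validation. The inflation is also modest: a useless marker would show sensitivity plus specificity of about 105.5%, which would mislead few readers. The AUC is reported too, and for a single marker it does not depend on the cut-off, so a weak marker would remain visible. The hypothesis-generating caveat further softens the consequence. All this limits the weight of the point. It does not remove it, because Appendix VI itself settles that accuracy is reported at the optimised cut-offs, and a caveat does not correct a bias.

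A reader might also infer that ROC analysis is run only for markers with a significant t-test, since it is introduced as building on significant group differences. The wording is loose and sets no explicit gate, so I do not treat it as one.

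**Conclusion.** The three detectable differences are wrong as printed. At the stated inputs and a two-sided 5% level they are 109 ng/L, 198 ng/L and 5.1 U/ml. The error is conservative and leaves the case for 550 patients intact; it is a matter of correct and reproducible documentation.

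The planned reporting of sensitivity and specificity is optimistic by roughly 4 to 5 points on their sum (about 3 to 5.5 across the range simulated), and most so for the weakest marker. That size assumes normal markers with equal SDs and the 367 to 183 split. The protocol itself allows for non-normal markers, so the amount could differ in practice. The direction follows from choosing and assessing the cut-off on the same patients.

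Both matters are worth correcting. Neither threatens the sub-study or the main trial.

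**What to change.** 1. In Appendix VI, section 4, change the detectable differences to 109 ng/L (cMyC), 198 ng/L (GDF-15) and 5.1 U/ml (ST-2). If the printed values were intended, state the alpha, expected sample loss or N that produces them. State also that the test is two-sided.
2. In the Statistical analysis subsection, add that sensitivity and specificity will be reported with bootstrap optimism correction, re-selecting the cut-off in every resample, for all three markers. The single-marker AUC can be reported as it is.

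The cost is a few lines of text and a resampling loop, with no extra patients or samples. The downside is that reported accuracy will be a few points lower, in results that the protocol already regards as probably hypothesis generating.
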